## 4.Data analysis and the calculation of sample size

**4.1 Null hypothesis:** The improvement of Cobb Angle of AIS patients in the Digital Care group (DCG) is less than or equal to the improvement of Cobb Angle of AIS patients in the Conventional Intervention group (CIG);

**4.2 Alternative hypothesis:** The improvement of Cobb Angle of AIS patients in the DCG group is better than that of AIS patients in the CIG group

## **4.3 Statistical Method**

The distribution of continuous variables was assessed using the Kolmogorov-Smirnov test, followed by verification through histograms and Q-Q plots. Demographic data were presented as mean (standard deviation) for continuous variables and as number (percentage) for categorical variables. Baseline demographic characteristics and engagement metrics between groups were compared using independent samples t-test or Mann-Whitney U test for quantitative variables, and Chi-square test or Fisher's exact test for categorical variables.

The effects of each intervention on primary and secondary outcomes were evaluated based on the 6-month endpoint outcomes and the changes between baseline and 6 months. Both intention-to-treat (ITT) and per-protocol analyses were conducted for outcome assessment. Missing data were handled using multiple imputation by chained equations (MICE).

Receiver operating characteristic (ROC) curve analysis was employed to determine the minimal clinically important difference (MCID) for improvement in Cobb angle post-PSSE intervention at 6 months, which was identified as 3.50 degrees. However, Charalampidis A et al. defined treatment success in patients with moderate idiopathic scoliosis as no progression in scoliosis in individuals with a Risser grade  $\leq 4$  after 6 months of PSSE intervention.

The primary and secondary outcomes of this study were reported as mean, standard deviation (SD), and 95% confidence interval (CI). Given the assumption of normality, primary and secondary outcomes were evaluated using the independent samples t-test. The proportion of patients who exhibited disease progression or improvement in Cobb angle between the two groups was compared using the Chi-square test.

179 All analyses were conducted under a two-tailed hypothesis with an alpha level of  
180 0.05. Statistical analyses were performed using SPSS (version 23.0, SPSS Inc.,  
181 Chicago, Illinois, USA), and were carried out by a blinded statistician

182

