## 3.3 The definition of outcomes

All subjects will undergo baseline measurements at the Department of Rehabilitation, Peking Union Medical College Hospital. After a 6-month intervention, all participants are required to return to the hospital for a 6-month follow-up assessment. The primary outcome measure is the change in the Cobb angle of the primary curve between baseline and the 6-month follow-up. The Cobb angle will be measured on standing radiographs by two physical therapists (PTs) who will determine the angle between the most tilted vertebrae at the upper and lower ends of the curve. The final Cobb angle will be the average of the two measurements. Secondary outcomes are listed in Table 5.

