## 183 **4.4 The calculation of sample size**

184 The sample size estimation for this study is based on the Cobb angle, which serves  
185 as the primary outcome measure. The sample size was calculated using PASS  
186 11.0 In accordance with the principles of clinical superiority trials and preliminary  
187 trial results, the clinically meaningful difference in the improvement of the Cobb  
188 angle between the DCG and CIG groups is 4, with a standard deviation of 6 for both  
189 groups, and a superiority margin of 4 for the Cobb angle. Assuming a power of 80%  
190 and a two-sided significance level of 0.05, the estimated sample size is 102  
191 participants (51 per group). Accounting for a 20% dropout rate, a total of 128  
192 participants (64 per group) will need to be enrolled.

193

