## 223 **6.Research process**

### 224 **6.1 The patients' baseline assessment**

- 225 (1) Complete basic information such as height, weight, age, and the Risser grade;
- 226 (2) Whether the individuals have disc herniation, nerve compression symptoms,
- 227 spinal fracture, etc., are determined by X-ray and physical examination;
- 228 (3) Baseline Cobb Angle, ATR, and the gait analysis will be assessed.

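### Section 4.3 does not say which of its unadjusted t-tests decides the primary outcome; one ITT analysis adjusted for baseline Cobb angle would settle this and gain some precision

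*Protocol*

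**What the plan says.** Protocol section 3.3 defines the primary outcome: "The primary outcome measure is the change in the Cobb angle of the primary curve between baseline and the 6-month follow-up". The alternative hypothesis in section 4.2 is on the same scale: "The improvement of Cobb Angle of AIS patients in the DCG group is better than that of AIS patients in the CIG group". Section 4.4 sizes the trial on the difference in improvement between the groups.

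Section 4.3 then sets the analysis:

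- Quantities: effects on primary and secondary outcomes "were evaluated based on the 6-month endpoint outcomes and the changes between baseline and 6 months".
- Sets: "Both intention-to-treat (ITT) and per-protocol analyses were conducted for outcome assessment". Missing data are handled by multiple imputation by chained equations.
- Test: "Given the assumption of normality, primary and secondary outcomes were evaluated using the independent samples t-test". No covariate is named.
- Level: "All analyses were conducted under a two-tailed hypothesis with an alpha level of" 0.05.

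Section 6.1 confirms that baseline values are available: "Baseline Cobb Angle, ATR, and the gait analysis will be assessed". Risser grade is recorded at the same visit.

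**The concern.** There are two separate matters.

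The first is which result decides the trial. Section 4.3 puts two analysis sets side by side at the same level, and also two forms of the outcome, without giving any of them precedence. If the results disagree, the text does not say which one answers the hypothesis in section 4.2. The choice of set matters here. Section 4.5 says therapists and patients cannot be blinded. The engagement entry in section 3.3 has adherence logged automatically in the digital arm and by hand in the conventional arm. Section 4.4 allows for 20% dropout. A per-protocol comparison could therefore drop different kinds of patients from each arm.

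The second is precision. The baseline Cobb angle is measured in everyone and is a natural covariate, but the named test uses it only by subtraction (for change) or not at all (for the 6-month value). Section 5.1 sets a lower Cobb limit and no upper one, so starting angles may vary widely.

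**Working it through.** **Inputs from the protocol.** Difference in improvement 4 degrees and SD 6 in each group (section 4.4, read as the SD of the change); 51 evaluable and 64 enrolled per group (section 4.4); two-sided 0.05 (sections 4.3 and 4.4).

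**Assumptions not in the protocol.** Equal SDs at baseline and 6 months; correlation rho between the two visits of 0.7 to 0.9, with a wider range where shown; per-protocol set a random 80% of ITT.

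**The plan's own figure.** Section 4.4 states: "a two-sided significance level of 0.05, the estimated sample size is 102". For a plain comparison of means, n per group = 2 x 6² x (1.960 + 0.842)² / 4² = 35.3, so 36, not 51. The dropout step does reproduce: 102 / 0.8 = 127.5, so 128. The mismatch in 51 is a separate matter. Here 51 serves only as the planned evaluable number.

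**Power of the t-test on change.** SE = 6 x sqrt(2/51) = 1.188. Power = Phi(4/1.188 - 1.960) = Phi(1.41) = 0.920 (0.915 by the exact t calculation).

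**Power of ANCOVA.** With equal visit SDs s, the change variance is 2s²(1 - rho) and the ANCOVA residual variance is s²(1 - rho²). Their ratio is (1 + rho)/2, so the ANCOVA SD is 6 x sqrt((1 + rho)/2).

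| rho | Variance saving | ANCOVA SD | Power at 51 per group | n per group for 80% power (change t-test: 36) |
|---|---|---|---|---|
| 0.7 | 15% | 5.53 | 0.955 | 31 |
| 0.8 | 10% | 5.69 | 0.944 | 32 |
| 0.9 | 5% | 5.85 | 0.932 | 34 |

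At lower correlations the gain is larger: power is 0.973 at rho 0.5 and 0.987 at rho 0.3.

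**Power of the unadjusted 6-month comparison.** The 6-month SD is 6 / sqrt(2(1 - rho)), which is 7.75, 9.49 and 13.42 at rho 0.7, 0.8 and 0.9. Power at 51 per group is 0.74, 0.57 and 0.33. It is 0.92 at rho 0.5 and 0.98 at rho 0.3, so the result depends heavily on an unknown. The correlation between the 6-month and change estimates is sqrt((1 - rho)/2), which is 0.39, 0.32 and 0.22 at rho 0.7, 0.8 and 0.9. The two analyses can readily disagree.

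**False-positive chance with no ranking.** Null trials were simulated with 64 per arm and complete data, 20,000 runs for each rho from 0.3 to 0.95. The chance that at least one two-sided test falls below 0.05 is:

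| What may count as success | Chance of at least one false positive |
|---|---|
| Change, ITT only | about 0.05 |
| Change, ITT or per-protocol | 0.069 to 0.075 |
| Change or 6-month value, ITT only | 0.089 to 0.097 |
| Any of the four | 0.125 to 0.136 |

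These figures count errors in both directions. They allow for the correlation between the tests; four independent tests would give 1 - 0.95⁴ = 0.185, which does not apply here.

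**The case against.** The strongest reply is that the primary variable is not in doubt. The outcome definition, the hypotheses and the sample-size section all refer to change or improvement, so the 6-month value is best read as supportive. That stands. A reader might infer from section 4.3 alone that the trial has four equal chances of success, at about 13%. Read as a whole, the protocol does not support this, and the main open choice is the analysis set. The sentence naming the t-test is also separate from the one naming the two quantities, so a confirmatory test of the 6-month Cobb angle is not strictly required by the text.

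A reader might also infer that the plan discards the baseline. For the declared primary it does not: a change score uses baseline by subtraction, and the same holds for the changes in trunk rotation and pelvic tilt. Only the 6-month comparison ignores it. An unadjusted t-test on change is valid in a randomised trial, and at 51 per group it already exceeds the planned 80% power under the stated difference and SD.

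The low power figures of 0.33 to 0.74 belong to a comparison that is not the primary one, and they rest on an assumed correlation and equal SDs. They are not evidence that the trial is underpowered.

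Finally, a separate analysis plan may exist, and covariates and the ranking of sets are often left to it. Their absence alone would not be a finding. But the protocol does more than stay silent: it names the t-test, both quantities and both sets. An analysis plan that adjusted for baseline would depart from that method, and one that ranked the sets would supply an order this text lacks.

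**Conclusion.** The point holds in limited form. Section 4.3 names ITT and per-protocol analyses of the primary outcome at the same level and does not say which decides. If either may carry the claim, the false-positive chance is about 7% against a nominal 5%, assuming a per-protocol set that is a random 80% of ITT. Exclusions that are not random would add bias that this figure does not include. About 13% applies only if the 6-month value also counts as a route to success, which the rest of the protocol argues against.

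The case for ANCOVA over the t-test on change is a modest gain in precision, not the correction of an invalid test. Variance falls by 15% to 5%, and power rises from about 92% to between 95% and 93%, for correlations of 0.7 to 0.9 with equal visit SDs. Neither assumption comes from the protocol. The change is worth making because the covariate is already collected and one sentence can settle both matters.

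**What to change.** In section 4.3, name one primary analysis: the ITT comparison, with patients as randomised and missing values multiply imputed as already planned, of primary-curve Cobb angle by ANCOVA on group and baseline Cobb angle. Report the adjusted difference with its 95% CI. With baseline in the model, the treatment estimate is the same whether the 6-month value or the change is the response, so this fits the outcome in section 3.3 and the hypotheses in sections 4.1 and 4.2.

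Label the per-protocol analysis, and the unadjusted t-tests on change and on the 6-month value, as supportive. Analyse trunk rotation and each pelvic tilt measure in the same way, adjusted for its own baseline. Risser grade may be added as a covariate but is optional.

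The cost is a few sentences in section 4.3, and the same statement in any separate analysis plan. No new data are needed, and the named software can fit the model.

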## 183 **4.4 The calculation of sample size**

184 The sample size estimation for this study is based on the Cobb angle, which serves  
185 as the primary outcome measure. The sample size was calculated using PASS  
186 11.0 In accordance with the principles of clinical superiority trials and preliminary  
187 trial results, the clinically meaningful difference in the improvement of the Cobb  
188 angle between the DCG and CIG groups is 4, with a standard deviation of 6 for both  
189 groups, and a superiority margin of 4 for the Cobb angle. Assuming a power of 80%  
190 and a two-sided significance level of 0.05, the estimated sample size is 102  
191 participants (51 per group). Accounting for a 20% dropout rate, a total of 128  
192 participants (64 per group) will need to be enrolled.

193

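### Section 4.4 gives 4° as both the difference and the superiority margin; 51 per group does not follow from the stated inputs, and the margin conflicts with the hypotheses and test in 4.1 to 4.3

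*Protocol*

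**What the plan says.** The sample size paragraph (protocol, section 4.4) bases the trial on the change in Cobb angle. It says that the clinically meaningful difference in improvement of the Cobb "angle between the DCG and CIG groups is 4, with a standard deviation of 6 for both" groups, and it adds a second quantity of the same size, followed by the power: "groups, and a superiority margin of 4 for the Cobb angle. Assuming a power of 80" per cent. With that power "and a two-sided significance level of 0.05, the estimated sample size is 102" participants, which is 51 per group. A 20% dropout allowance raises this to 128, or 64 per group.

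The margin appears nowhere else. Under the null hypothesis in section 4.1, improvement in the digital group "is less than or equal to the improvement of Cobb Angle of AIS patients in the Conventional Intervention group (CIG"), so the boundary is zero. The alternative in 4.2 claims only that the digital group does better. In section 4.3, "primary and secondary outcomes were evaluated using the independent samples t-test", two-tailed at 0.05, with no shift of the null value.

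**The concern.** A test of superiority by a margin is powered on the assumed true difference minus the margin. When both are 4°, nothing is left to detect, and no number of patients gives 80% power. If the margin is set aside, the stated inputs should lead to fewer than 51 per group. On both readings, the sample size and the power do not belong together.

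The larger stake is the success rule. Sections 4.1 to 4.3 call the trial positive if the difference is shown to exceed 0. Section 4.4 implies that it must be shown to exceed 4°. The same result could be declared positive or negative depending on which section is followed, and a choice made after seeing the data would be post hoc.

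**Working it through.** **Inputs, all from section 4.4 unless noted.** Difference 4°; SD 6° in each group; margin 4°; power 80%; two-sided alpha 0.05; 1:1 allocation; 51 evaluable per group; dropout 20%. Null boundary 0 (section 4.1). Two-tailed independent samples t-test (section 4.3).

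**1. The plan's own figure, with the margin as written.** For superiority by a margin, n per group = 2 × [SD × (z for alpha + z for power) / (difference − margin)]². The denominator is 4 − 4 = 0, so n is undefined. Power equals the type I error in the favourable tail, 2.5%, whether n is 51, 64, 500 or 100,000 per group. The figure of 51 is not reproduced.

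**2. The same inputs with the null boundary at 0.** n = 2 × [6 × (1.960 + 0.842) / 4]² = 35.3, hence 36 per group by the normal approximation. By the noncentral t distribution, 36 per group give 79.7% and 37 give 80.8%, so 37 are needed. The figure of 51 is again not reproduced; the gap of 14 per group is not rounding.

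**3. Power of the stated size against the zero null (t-test, SD 6, two-sided 0.05).**

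| Per group | True difference | Power |
|---|---|---|
| 51 | 4° | 91.5% |
| 64 | 4° | 96.3% |
| 51 | 3.5° (the MCID in section 4.3) | 83% |
| 51 | 3.36° | 80% |

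**4. Can the source of 51 be found?** Other standard variants that keep a difference of 4° and SD 6 also miss it: one-sided 0.05 gives 29 per group; 90% power two-sided gives 49; 95% power gives 60 two-sided and 50 one-sided. Several changes to the stated inputs do give about 51 at 80% power: an SD of about 7.1 with a 4° difference, two-sided; a net difference of about 3.36° with SD 6, two-sided; or a net difference of 3° with SD 6, one-sided 0.05. That last net difference could come from a difference of 4° and a margin of 1°, or from a difference of 7° and a margin of 4°. Each departs from at least one stated input, and nothing in the protocol favours one over another.

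**5. The two success rules.** With 51 per group, SE = 6 × √(2/51) = 1.188°, and the t critical value on 100 df is 1.984.
- Zero boundary (4.1 to 4.3): the observed difference must exceed 1.984 × 1.188 = 2.36°.
- Margin of 4° (4.4): the observed difference must exceed 4 + 2.36 = 6.36°.

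The rules disagree for every observed difference between about 2.4° and 6.4°. That band contains the planned 4° itself.

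**6. Dropout step.** 102 / 0.8 = 127.5, rounded up to 128, or 64 per group. This is correct.

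**The case against.** Three points can fairly be made for the plan.

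First, section 4.4 calls 4° the clinically meaningful difference, not the expected true effect. The difference and the margin could be one quantity stated twice, with the expected effect, perhaps from the preliminary results that the section mentions, left out. This stands as a limit: the statement that no sample size suffices holds only if 4° is the assumed true difference. It does not rescue the paragraph, because the protocol gives no other effect size for the calculation.

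Second, a reader might infer that the trial is underpowered. The documents do not support that. The hypotheses and the test agree on a zero boundary, and for that test 51 per group exceed the 80% target at 4° and still give about 83% at 3.5°.

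Third, a reader might infer that 51 arose from a margin of 1° and a one-sided test, since those values reproduce it exactly. Other altered inputs do so equally well, so this is a guess. The supportable statement is that the stated inputs do not give 51.

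A margin that occurs in a single clause and in neither the hypotheses nor the analysis also looks like a drafting slip. That is plausible, but the text as it stands still carries two success rules.

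**Conclusion.** The point holds, within limits. Section 4.4 conflicts with its own inputs and with sections 4.1 to 4.3. As written, with 4° taken as the assumed true difference, the calculation has no solution. Without the margin it should give 37 per group, and the stated 51 carry 91.5% power, not 80%. The conflict over success covers observed differences from about 2.4° to 6.4° at 51 per group, assuming SD 6 in both groups.

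The fault is a wrong sample size and power statement together with an unsettled success criterion. It is not a shortage of patients for the test that the protocol specifies. It should be corrected before the analysis, because the primary conclusion depends on which section is followed.

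**What to change.** First, check the inputs actually entered in the sample size software (true difference, margin, SD, sidedness), and then make sections 4.1 to 4.4 agree before the analysis.

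- **Unless a margin was truly intended:** remove the margin of 4 from section 4.4, keep 128 enrolled, and state one success rule: the two-sided 95% confidence interval for digital minus conventional improvement lies above 0. Restate the power along these lines: 51 evaluable patients per group give about 91.5% power for a 4° difference (SD 6, two-sided 0.05), or 80% power for about 3.4°.
- **If a margin was intended:** it must be smaller than the assumed true difference, appear in 4.1 and 4.2, and be tested against the lower confidence limit. The power must then be restated for the enrolled size.

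The first option changes wording only and needs no extra patients. Under the second, the restated power will show whether 128 are enough.

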## 194 **4.5 The method of Allocation**

195 Participants were randomly allocated to either the TBEG group or the OBEG group  
196 using an online platform (<https://www.random.org/>). Subsequently, subjects in the  
197 OBEG group were assigned the letter "C," while those in the TBEG group were  
198 assigned the letter "T." Based on the results generated by the online platform (e.g.,  
199 C, T, C, T, T, C, ...), slips of paper labeled with the letters "T" and "C" were  
200 placed in sealed, opaque, and uniformly sized envelopes. After all baseline  
201 measurements were completed for the study subjects, the envelopes were  
202 sequentially opened to reveal the allocation results. The allocation sequence was  
203 prepared by an independent researcher, not involved in the study, using a block  
204 randomization model. Given the nature of the intervention, it was not feasible to  
205 blind the physical therapists and patients to the allocation results.

206

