## 1. Background

Adolescent idiopathic scoliosis (AIS) is a complex three-dimensional spinal deformity of unknown etiology, defined as a spinal curvature of  $\geq 10^{\circ 1, 2}$ . According to scoliosis screening studies conducted between 1985 and 2011, the prevalence of AIS is estimated to be between 0.5% and 5.2%. It is generally accepted that the incidence of AIS among individuals under the age of 16 is approximately 2% to 3%. Among adolescents with a Cobb angle greater than  $20^{\circ}$ , the likelihood of disease progression is 70% or more. According to the recommendations of the International Society on Scoliosis Orthopaedic and Rehabilitation Treatment (SOSORT), conservative treatment should be provided to adolescents with AIS to prevent the progression of scoliosis before skeletal maturity is reached.

Physiotherapy Scoliosis-Specific Exercises (PSSE) are among the most crucial conservative treatments for patients with AIS. Moderate-certainty evidence from multiple randomized controlled trials (RCTs) supports the effectiveness of PSSE in slowing the progression of scoliosis in AIS patients and even reducing the degree of curvature. However, compared to conventional exercises such as resistance training, PSSE requires a deeper understanding by patients of the specific exercises tailored to their type of scoliosis, making mastery more complex and challenging for AIS patients. Additionally, patients with AIS must adhere consistently to a standardized PSSE regimen over the long term and develop habits of daily self-management to ensure the efficacy of PSSE. In previous high-intensity evidence-based trials, the traditional PSSE model involved an initial assessment and 1 to 3 treatment sessions conducted by qualified physiotherapists at outpatient clinics or specialized orthopedic institutions, after which patients completed the PSSE regimen at home without supervision.

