## 207 **5.Exclusion and Inclusion criteria**

### 208 **5.1 Inclusion criteria**

209 The inclusion criteria were as follows:

210 (a) untreated adolescent males and females with AIS;

- 211 (b) AIS patients with a primary curve Cobb angle  $>10^{\circ}$  ;
- 212 (c) all subjects aged 9 to 17 years;
- 213 (d) AIS patients with a Risser grade ranging from 0 to 4, with female adolescents
- 214 being within one year post-menarche;
- 215 (e) participants capable of understanding and completing complex motor tasks;
- 216 (f) patients or their parents proficient in using a smartphone.

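### Baseline Cobb angle and Risser grade are known before allocation but used neither to stratify it nor as covariates, so chance imbalance goes uncorrected and some precision is lost

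*Protocol*

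**What the plan says.** **Prognosis.** Protocol section 1 says that in adolescents with a Cobb angle above 20° "the likelihood of disease progression is 70% or more". It also says that conservative treatment is given "to prevent the progression of scoliosis before skeletal maturity is reached". The first statement ties risk to curve size explicitly. The second implies that growth stage matters but gives no risk by Risser grade.

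**Eligibility.** Section 5.1 admits ages 9 to 17 and any primary curve above 10°, with no upper limit. It also admits "AIS patients with a Risser grade ranging from 0 to 4, with female adolescents" "being within one year post-menarche".

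**Baseline data.** Section 6.1 has staff "Complete basic information such as height, weight, age, and the Risser grade" and also measure the Cobb angle. Section 4.5 has the envelopes opened only after all baseline measurements, so both factors are known in time.

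**Allocation.** Section 4.5 describes a blocked list, "prepared by an independent researcher, not involved in the study, using a block" randomisation model, in sealed opaque envelopes opened in sequence. No stratification factor is named.

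**Analysis.** Section 4.3 states that "primary and secondary outcomes were evaluated using the independent samples t-test", given normality, and that the proportions progressing or improving are compared by Chi-square test. Neither comparison has a covariate. In that section Risser grade appears only in another trial's definition of treatment success.

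**The concern.** The trial enrols patients on both sides of the 20° threshold that the protocol itself uses to mark high risk, and across most of the skeletal maturity scale. Their expected six-month course is therefore likely to vary whatever the arm. Blocking balances numbers per arm, not severity or growth stage. Using the change in Cobb angle subtracts the baseline value, but it does not adjust for a rate of progression that depends on curve size or maturity.

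Two things are at stake, and both come from the same source. If one arm happens to receive more patients at high risk of progression, the reported difference carries that imbalance, and the stated analysis has no means of removing it. Section 4.3 plans baseline comparisons between groups but gives no rule for acting on what they show. In addition, outcome variation that the baseline factors could explain stays in the error term and widens the interval.

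**Working it through.** **The plan's own figure.** Section 4.4 gives a difference of 4°, SD 6°, two-sided alpha 0.05, 80% power, 51 per group, and 64 per group after 20% dropout. The usual formula gives n = 2 × 6² × (1.960 + 0.842)² / 4² ≈ 35.3, so 36 per group (37 with the exact t distribution), not 51. With the stated superiority margin of 4° equal to the difference of 4°, no finite n exists. The dropout step does reproduce: 51 / 0.8 = 63.75, rounded up to 64. The mismatch is a separate issue. Only the SD of 6° and the arm sizes are used below.

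**Chance imbalance.** Assume a binary factor present in 64 of the 128 patients. The number k falling in one arm is hypergeometric (128, 64, 64), and the difference in share is |2k − 64| / 64.
- 10 points or more means |k − 32| ≥ 4: probability 0.216.
- 20 points or more means |k − 32| ≥ 7: probability 0.021.

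Treating the arms as independent binomials with prevalence 30% to 50% gives 21% to 25% for 10 points or more at 64 per arm, and 23% to 28% at 51 per arm.

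**What adjustment is worth.** Let d be the difference in mean six-month Cobb change between low- and high-Risser patients, half in each group. The protocol gives no value, so d is varied from 1 to 6°. Share of variance explained: R² = 0.25 d² / 36. Interval width after adjustment: √(1 − R²) of the original. Shift from a 10-point imbalance: 0.10 d.

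| d (assumed) | R² | Interval narrower by | Shift at 10 points |
|---|---|---|---|
| 1° | 0.7% | 0.3% | 0.1° |
| 2° | 2.8% | 1.4% | 0.2° |
| 3° | 6.3% | 3.2% | 0.3° |
| 4° | 11.1% | 5.7% | 0.4° |
| 6° | 25.0% | 13.4% | 0.6° |

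For scale, the standard error of the difference is 6 × √(2/64) = 1.06° at 64 per arm and 6 × √(2/51) = 1.19° at 51, and the planned difference is 4°.

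**Validity of the unadjusted test.** Null trials were simulated with 51 per arm, a factor in half of patients, d = 4° and total SD 6° (residual variance 36 − 0.25 × 16 = 32). Four runs of 200,000 trials gave rejection rates of 0.049 to 0.050. A preliminary run of 20,000 had given 0.055, which the 800,000 later trials do not bear out. The 5% level holds.

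**The rate given a particular imbalance.** By normal approximation at 64 per arm, the test rejects when the difference exceeds 1.96 × 1.06 = 2.08°. Given the imbalance, the difference is centred on the shift, with standard error 1.06 × √(1 − R²). For d = 6° and 20 points, the shift is 1.2° and the standard error 0.92°, so the upper tail alone is P(Z > (2.08 − 1.2) / 0.92) ≈ 0.17. For d = 1° and 20 points the rate is about 5%. At 10 points it stays near 5% even for d = 6° (about 5.6%).

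**The case against.** Unstratified blocked randomisation with concealed envelopes is a valid design, and nothing in sections 4.3 and 4.5 is contradictory. The standard error already contains the Risser-driven spread, because an SD of 6° describes all enrolled patients. A shift of 0.1 to 0.6° lies within that error and is small against 4°. The shift and the wider interval are one chance variation seen two ways, not two separate harms. The menarche limit already narrows maturity among girls. All of this stands, and it caps the size of the point.

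It can also be said that covariates belong in a statistical analysis plan, which is not shown. That carries less weight here: the protocol does not leave the method open but names a t-test and a Chi-square test.

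Several stronger readings are tempting, and the protocol does not support them.
- *The comparison is biased.* Under concealed 1:1 randomisation the arms differ in natural course only by chance. The estimate is unbiased on average and the test keeps its level.
- *Without an untreated arm, natural course cannot be separated from treatment effect.* The question is digital care against conventional care. A third arm would not correct an imbalance between those two.
- *The protocol itself says that risk depends on Risser grade.* It says so only for curve size; growth stage is implied.
- *Risser grade is used only in the baseline table.* The protocol does not say this. Risser grade is absent from the stated comparisons, and no more can be established.
- *At least one of two factors is imbalanced in 39% of trials.* From 1 − (1 − 0.216)² = 0.385, this needs Cobb angle and Risser grade to be independent, which nothing in the protocol shows.

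**Conclusion.** The point holds as a matter of precision and protection against chance imbalance. Two factors that the protocol treats as prognostic, one explicitly and one by implication, are measured before allocation and then appear in neither the allocation nor the stated tests. A 10-point imbalance in one such factor is expected in roughly one trial in five (assuming prevalence of one half and 64 per arm). The unadjusted test would be materially misleading only under a large and uncommon imbalance, about 20 points (2% of trials), combined with a strong Risser effect.

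The gain from adjustment runs from negligible (interval 0.3% narrower at d = 1°) to useful (13% narrower at d = 6°). Where it falls depends on d, for which the protocol offers no figure. The upper end is generous, since 6° equals the whole SD and exceeds the planned difference. The case for change rests less on the size of the gain than on its low cost, and on fixing the covariates before the data are seen.

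**What to change.** **Main change, section 4.3.** Replace the unadjusted t-test for the primary outcome with a pre-specified ANCOVA of the six-month Cobb angle (or its change) on group, baseline Cobb angle and baseline Risser grade. Analyse the proportion progressing with a model using the same covariates, such as logistic regression. Both covariates are already collected, so the cost is slightly more analysis work. This can be done whether or not enrolment has begun, provided it is fixed before the outcome data are compared.

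**Optional, section 4.5, only if enrolment has not begun.** Have the independent researcher prepare separate blocked envelope sequences by baseline Cobb angle (up to 20°, above 20°) and, if wanted, by a Risser cut chosen by the investigators; the protocol supplies no basis for a particular cut. Include the stratification factors in the model. The costs are more envelope sets, arm sizes that may end slightly unequal because of incomplete blocks, and some risk of drawing from the wrong set. If enrolment has begun, keep the sequence and rely on the covariates.
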